### Validity and reliability / rigour

This study uses a rigorous study design, i.e., a RCT with a CG and stratified randomization. For outcome evaluation, a range of measures with high validity and reliability will be used. One measure, the *Attitudes Towards Medical Communication Scale* [39],will be translated into German using the TRAPD translation protocol [36] and psychometrically tested in parallel to the RCT. Additionally, we will conduct cognitive interviews for all translated and adapted measures to ensure comprehensibility by the target group. Furthermore, the measures as well as the newly developed CST will be pre-tested in a sample, which will be comparable to the target group. Single items as well as the SPAs will be developed by the research team according to the trainings’ content and pre-tested. Blinded double data entry of quantitative data will be performed. The study team was supported by an independent advisory board of international experts specialized in healthcare communication. For preparing this study protocol, we followed the Standard Protocol Items: Recommendations for Interventional Trials 2013 (SPIRIT 2013) [50].

## Discussion

This study closes the research gap of a needs-based developed and systematically evaluated CSTs for nursing professionals in Germany. Since this patient-centered CST was developed according to previously analyzed needs of nurses, it will directly address communicative challenges of their daily work routine. We expect to improve self-efficacy regarding communication, communication skills and mental burden of participating nurses. Furthermore, we will derive indications for future implementation of the CST into routine clinical practice. In case of a proven effectiveness of the CST for nurses, an implementation in diverse clinical settings (including e.g. geriatric or rehabilitation facilities) should be conducted and evaluated in future implementation studies. Thereby, additional and more distant implementation outcomes, especially the impact on patient-related outcomes (e.g. satisfaction with communication with HCPs, anxiety) could be addressed as they are not part of the study at hand. Finally, our results may be useful for other health care institutions and implementation researchers when planning or implementing CST for nurses.

### Dissemination

Results of this study will be presented at national and international conferences. Furthermore, results will be published in relevant journals (peer reviewed, open access) to ensure accessibility for clinicians, researchers and other stakeholders, including patients. Press releases, in-house newsletters and social media will also be used for dissemination. In addition, a project website provides information about study progress (UKE - Institut und Poliklinik für Medizinische Psychologie - KOMPAT Projekt).

### Limitations

There will be several limitations of this study. First, it is a single-center study conducted at one academic medical center in Germany. Thus, generalizability to other healthcare settings and/or other countries is limited and should be analyzed in future studies. Second, our sampling approach might lead to a self-selection bias of participants, who are specifically interested in the topic. To improve diversity of the sample, we will ensure to include participants of diverse clinical backgrounds and work experience. We plan to apply stratified randomization, where participants will be randomized within strata (i.e., departments of the UKE). Thus, there will be a chance of contamination within these groups as participants of the IG and CG might work closely together within a ward. To reduce contamination processes to a minimum, participants of both groups will be informed about disadvantages of contamination for the study’s results and will be asked not to share content of the training or the evaluation with other colleagues. Additionally, the evaluation questionnaire will contain one item on contamination to include this factor as a covariate in the statistical outcome evaluation if necessary.

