#### Recruitment and randomization

Nurses will be recruited continuously starting in November 2022 until spring 2024 within their departments. Therefore, we contact heads of relevant departments at the UKE by e-mail and ask them to forward the study information to all eligible staff in the respective department. Prior to study participation, eligible nurses will be informed that there is an equal chance to be assigned to the IG or CG. After giving informed written consent, they will be asked to complete the baseline assessment (t0). Afterwards, participants will be randomized in a 1:1 ratio to either IG or CG. For this purpose, stratified randomization will be applied [30]. Each department of the UKE will be defined as a stratum. A member of the research team, who will not be involved in recruitment of eligible nurses, will allocate participating nurses within each stratum to either IG or CG by using permuted blocks. Participating nurses of the CG are offered to participate in the training after data collection has been completed.

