**Level 4****: ****Results** (What is the impact of the CST on participants’ work-related mental burden?)				
Professional fulfillment (PFI-G)		X	X	X
Depression & anxiety (PHQ-4)		X	X	X
Subjective working capacities (dimension 1 and 2 of WAI)		X	X	X
**Covariate** (What factors may have an influence on the results of the four levels?)				
Impact of contamination (self-developed)	IG	X		
	CG	X	X	X
Perceived person-centeredness of healthcare settings (EPAT, short version)		X		X

*CG* waitlist-control group, *CST* communication skills training, *EPAT* Experienced Patient-Centeredness Questionnaire, *IG* intervention group, *PFI-G* German version of Professional Fulfillment Index, *PHQ-4* Patient Health Questionnaire 4, *PTA* Performance Test Anxiety, *SE-12-G* German version of Self-Efficacy of Communication Skills Scale, *SPA* standardized patient assessment, *WAI* Work Ability Index

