#### Primary outcome

As the primary outcome, we chose self-efficacy regarding nurses’ communicating with patients. According to Albert Bandura (1997) self-efficacy is the belief in one's own ability to successfully deal with certain tasks or situations [32]. *S*elf-efficacy has been shown to be positively related to HCPs’ performance in communication [33]. Thus, the concept of self-efficacy has been frequently used to assess the impact of CST on HPs [11, 33, 34]. Self-efficacy regarding communication skills with patients will be assessed using the German version of the 12-item *Self-Efficacy of Communication Skills scale (SE-12).* The original scale was developed by Axboe et al. [35] and has already been used as primary outcome in other studies to evaluate CSTs for nurses [11]. Items on this one-dimensional scale can be answered on a scale from 1 (“very uncertain”) to 10 (“very certain”) with an additional option to rate items as “not relevant”. In a previous study by the research team, the SE-12 was translated and adapted into German following the team approach consisting of translation, review, adjudication, pretesting and documentation (TRAPD) [36] and psychometrically tested by Frerichs et al. [37]. Self-efficacy will be assessed at all measurement points (t0, t1, t2), with t1 being the primary endpoint.

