##### Impact of contamination

To measure the impact of contamination, a self-developed item will assess the extent to which participants from CG have received information about the trainings’ content from colleagues of the IG. This item will be assessed in the CG at all measurement points (t0, t1, t2) and in the IG only at baseline (t0).

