### Data analysis

Prior to analysis of quantitative data, a missing data analysis will be conducted and cut-off criteria for including instruments in analysis will be applied. Multiple imputation will be used to handle remaining missing data. Descriptive outcome analysis and process evaluation will be performed by calculating frequencies and percentages for categorical data, medians and interquartile ranges for ordinal or non-normally distributed quantitative data, and means and standard deviations for approximately normally distributed data. Quantitative outcomes will be analyzed by linear mixed models including treatment group, time, and their interaction as fixed effects. Hierarchical data structures (e.g., clustering within departments) will be accounted for by letting the intercept vary randomly across clusters. Categorical and ordinal outcomes will be analyzed by corresponding models which use an appropriate link (e.g., logistic for binary variables). We will report 95 percent confidence intervals for all estimated parameters. The level of statistical significance for the primary confirmatory analysis will be set at p<.05. All other analyses will be considered exploratory. Qualitative data of the process evaluation will be analyzed according to principles of content analysis [49]. Quantitative data of outcome and process evaluation will be entered into and analyzed with SPSS (IBM SPSS Statistics, V.23) by members of the research team consecutively. To ensure high data quality, 20% of the quantitative data will be entered double for quality control. Qualitative data of process evaluation will be imported into and analyzed with MAXQDA software (VERBI GmbH, Berlin, Germany).

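### The option to adjust outcomes for contamination relies on an item that, after randomisation, is collected only in the control group; if used, it does not estimate the as-randomised effect

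*Protocol article*

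**What the plan says.** All references are to the protocol article.

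- **Planned use.** Under Limitations, the article notes that randomising within departments lets nurses of both groups work side by side. It then allows the contamination item to enter the analysis: "the evaluation questionnaire will contain one item on contamination to include this factor as a covariate in the statistical outcome evaluation if necessary". Table 1 also lists the item among the covariates.
- **What the item asks.** Under Impact of contamination, it records how far "participants from CG have received information about the trainings’ content from colleagues of the IG".
- **Who is asked, and when.** The same section says: "This item will be assessed in the CG at all measurement points (t0, t1, t2) and in the IG only at baseline (t0"). Table 1 agrees.
- **Order of events.** Under Recruitment and randomization, consent and the t0 assessment come first: "Afterwards, participants will be randomized in a 1:1 ratio to either IG or CG". Self-efficacy (SE-12) is the primary outcome, "with t1 being the primary endpoint".
- **Model.** Data analysis specifies linear mixed models with group, time and their interaction, plus random intercepts for clusters. Contamination is not among the listed terms. The section adds: "Multiple imputation will be used to handle remaining missing data". Everything outside the primary confirmatory analysis is called exploratory.

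**The concern.** A covariate in a comparison of arms has to exist in both arms, and it should not be something that happens to one arm after allocation. At t1 and t2 this item fails both conditions. It is absent by design in the IG, and in the CG it reflects which nurses sought out or were told about the training content. Such nurses may differ in confidence from their colleagues whether or not the training works.

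Entering the item therefore does not clean contamination out of the treatment effect. It replaces the comparison of the two randomised groups with a comparison against a part of the control group selected after randomisation. The article does not say which time point would be used, how IG nurses would be coded, or what would make the adjustment necessary. As written, that choice could follow sight of the data. This goes beyond missing detail, because the stated purpose conflicts with the stated collection schedule. Filling in the details would not resolve it unless the covariate use is withdrawn or the method replaced.

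**Working it through.** **Background figure.** The stated 64 per group for d = 0.50, two-sided alpha 0.05 and power 0.80 reproduces (exact t-test: 63.77, rounded up to 64; power 0.801). The point below does not affect it.

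**Step 1: complete cases.** Every IG nurse lacks the item at t1 and t2, so all IG rows drop out. The design matrix (intercept, group, baseline, contamination) has rank 3 of 4, and the group effect is not estimable.

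**Step 2: filling in the IG.** Notation, in SD units:
- p: share of the CG contaminated
- τ: training effect against an untouched control
- k: share of τ that a contaminated control gains
- δ: SE-12 difference between nurses prone to contamination and the others that is unrelated to training and remains after whatever the model adjusts for

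Randomisation gives the IG the same share p of such nurses. The group coefficient then estimates:
- as randomised, item left out: τ − pkτ
- IG coded 0 (all IG against uncontaminated CG): τ + pδ
- IG coded 1 (all IG against contaminated CG): τ(1 − k) − (1 − p)δ

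The article gives none of p, k or δ. Take p = 0.30, k = 0.5 and τ = 0.50 as assumptions. As randomised: 0.50 − 0.30 × 0.5 × 0.50 = 0.425. For p = 10% and 50% it is about 0.48 and 0.37.

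Simulation at 90 per arm, with contamination driven by a trait that baseline does not capture (δ of about ±0.6, since 0.18 / 0.30 = 0.6):

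| Handling of IG values | Contamination unrelated to confidence | More confident nurses contaminated | Less confident nurses contaminated |
|---|---|---|---|
| Item left out | 0.43 | 0.43 | 0.42 |
| IG coded 0 | 0.50 | 0.69 | 0.31 |
| IG coded 1 | 0.25 | −0.18 | 0.68 |
| IG imputed from CG relation | 0.41 | 0.35 | 0.40 |
| IG coded 0, no training effect | 0.00 | +0.18 | −0.18 |

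The formulas agree. IG coded 0 gives 0.50 ± 0.30 × 0.6 = 0.68 or 0.32. IG coded 1 gives 0.25 ∓ 0.70 × 0.6 = −0.17 or 0.67.

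**Step 3: direction.** With no training effect and IG coded 0, the bias is pδ and takes the sign of δ. With a true effect, the departure from the as-randomised contrast is (τ + pδ) − (τ − pkτ) = p(δ + kτ). It is downward once δ falls below −kτ, here −0.25.

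**Step 4: size, and the role of baseline SE-12.** Take no training effect, IG coded 0, p = 0.30, and contaminated nurses 0.3, 0.5 or 0.8 SD more self-efficacious at both t0 and t1.
- *Without baseline:* 0.30 × 0.3, 0.5 and 0.8 = 0.09, 0.15 and 0.24. For the middle case, SE = √(1/90 + 1/63) = 0.164 and 0.15 / 0.164 = 0.91, so type I error is about 15%. Simulation gives about 8%, 15% and 28%.
- *With baseline:* if the t0–t1 correlation ρ is 0.5 to 0.7 (assumed), about pδ(1 − ρ) remains. The extremes are 0.30 × 0.3 × 0.3 = 0.027 and 0.30 × 0.8 × 0.5 = 0.12. Simulation gives about 0.02 to 0.11, with type I error about 6 to 12%. For the largest case, SE = 0.164 × √(1 − 0.25) = 0.142 and 0.11 / 0.142 = 0.77, which gives about 12%.
- *With a true effect of 0.50 and baseline in the model:* 0.50 + (0 to 0.11) = 0.50 to 0.61, against 0.425 as randomised.

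**The case against.** The other side has several good points.

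- **It is a contingency, not the main analysis.** A reader might infer that the randomised comparison of the primary outcome is lost. The article does not support that. The model under Data analysis omits contamination, the adjustment is conditional, and all but the primary analysis is exploratory. This stands: harm arises only if the option is used. But nothing keeps the option away from SE-12, and the article itself expects contamination within wards.
- **The t0 item is a valid covariate.** It is asked in both arms before randomisation, and with continuous recruitment later entrants may already have heard content. This stands, but it does not rescue the stated purpose. The Limitations section is concerned with IG and CG colleagues sharing content after allocation, which a pre-randomisation value cannot capture.
- **The bias need not favour the training.** A reader might infer that it is always upward. The calculations show both signs.
- **Type I error of 15 or 28% is overstated for this trial.** Those figures come from a model without baseline SE-12, whereas the planned model includes t0. A mixed model of t0 and t1 with a participant intercept (assumed) and time-varying contamination gives bias of about 0.03 to 0.12 and type I error of about 5 to 12%. Entered as a time-constant main effect, contamination leaves the group-by-time term almost unbiased. This stands, and the smaller figures are the ones to use.
- **30% may be high at t1.** The assessment directly follows the training, and participants are asked not to share content. This is fair; the bias shrinks in proportion to p.

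**Conclusion.** The point holds as a conditional one. The protocol article offers an adjustment that its own collection schedule cannot support. With the t1 or t2 item, the effect is either not estimable or set by how missing-by-design IG values are filled in, and it no longer estimates the difference between the groups as randomised.

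With IG coded 0 and no training effect, the bias is upward if more confident nurses become contaminated and downward if less confident ones do. With baseline SE-12 in the model, a plausible size is about 0.02 to 0.11 SD, with type I error of about 6 to 12% instead of 5%. With a true effect of 0.5 SD and half carry-over, the estimate is about 0.50 to 0.61 against about 0.43 as randomised, when contaminated nurses are equally or more confident. If baseline does not capture what drives contamination, the distortion can be larger, as Step 2 shows. The contamination rate, carry-over, confidence difference and t0–t1 correlation are all assumptions. The conflict between planned use and collection schedule does not depend on them.

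**What to change.** Replace the conditional sentence under Limitations and add to Data analysis:

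1. The confirmatory SE-12 analysis compares the randomised arms and does not include the t1/t2 contamination item.
2. Contamination at t1 and t2 is reported descriptively in the CG.
3. Any estimate of the effect without contamination is a labelled sensitivity analysis, specified in advance with its assumptions. One example is an instrumental-variable (CACE) analysis with randomised arm as instrument. The exposure given to a contaminated control must be fixed beforehand, because it drives the result. In the example above, counting contamination as full training gives 0.425 / (1 − 0.30) = 0.61, while counting it as half gives 0.425 / (1 − 0.15) = 0.50.
4. Only the t0 item may serve as a covariate, and only if that is decided in advance.

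The cost is a few sentences. No new data are needed and the sample size is unchanged. The downside is that the as-randomised estimate will be somewhat smaller if contamination occurs.

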## Conclusion

This is the first study systematically evaluating a needs-based patient-centered CST for nursing professionals in Germany. Results will give insights into effects of the training on self-efficacy, communication behavior and mental burden as well as other relevant outcomes. A thorough process evaluation will help to derive initial indications for future implementation of the training.

## Data Availability

Not applicable.

## Abbreviations

ATMCS: Attitude towards medical communication scale
C-CG: Calgary-Cambridge Guide
CFIR: Consolidated Framework for Implementation Research
CG: Waitlist-control group
CST: Communication skills training
EPAT: Experienced Patient-Centeredness Questionnaire
HCP: Healtcare professional
IG: Intervention group
PFI: Professional Fulfillment Index
PHQ-4: Patient Health Questionnaire-4
PTA: Performance Test Anxiety Questionnaire
RCT: Randomized Controlled Trail
SE-12: Self-Efficacy of Communication Skills Scale
SPA: Standardizedd Patient Assessment
SPIRIT: Standard Protocol Items: Recommendations for Interventional Trials
TFAI: Three-Factor Anxiety Inventory
TRAPD: Translation, Review, Adjudication, Prestest, Documentation
UKE: University Medical Center Hamburg-Eppendorf
WAI: Work Ability Index
